## Primary study parameter(s)

The mean and standard deviation of the segment intervals and the amplitudes (with 95% confidence intervals) and the heart axis of healthy fetuses without known CHD.

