# 2. OBJECTIVES

Primary Objective: To establish the normal ranges or values of amplitudes, segment intervals (with 95% confidence intervals) and the heart axis of the fECG in a healthy fetus.

Secondary Objective: To compare the fECG in various forms of severe CHD with the “normal” fECG. To determine the diagnostic value of fECG to detect CHD.

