# 3. STUDY DESIGN

Both the cross-sectional and case-cohort study are prospective in nature. In the future, a longitudinal cross-sectional study can be performed based upon this study.

The cross-sectional study will take place in the MMC, Veldhoven, the Netherlands and Diagnostic center Eindhoven, the Netherlands. All the patients who visit the outpatient clinic for the first time will receive information about the research. Patients who visit the Diagnostic center Eindhoven will receive information about the research via their appointment confirmation e-mail. Measurements will be performed before or after the SEO or GUO-1 after written informed consent; patients do not have to come to the hospital or the diagnostic center for an extra visit.

The case-cohort study will take place in the MMC Veldhoven, and the medical centers Radboud MC Nijmegen, Academic Medical Center Amsterdam, and Maastricht UMC the Netherlands. Whenever a patient is diagnosed with a fetal severe CHD in any of these centers by using the SEO and the GUO, they will inform the patient about our research and contact us after informed consent. We will perform a fECG during routine follow up visits in those centers. For more information on recruiting the patients, see chapter 9, paragraph 9.2 “Recruitment and consent”.

In the cross-sectional study, 200 pregnant women will be included. With this amount of patients, we can determine with the wanted accuracy what the normal values and 95% CI of a healthy fetus are^9, 10^. If any of these fetuses is diagnosed with a CHD, they will automatically be evaluated in the case-cohort study.

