In the case-cohort study, we will include pregnant women carrying fetuses with a form of severe CHD, preferably with the same CHD. A severe CHD is defined as possibly life threatening and/or needing intervention or surgery in the first year of life. For now, we believe that of every CHD, we need 10 patients to determine the difference between the normal values and the segment intervals of the fetuses with this severe CHD. The overall incidence of CHD is 4 to 9 per 1000 living newborns^4^. Because of this low incidence, it would take years to include more than 10 fetuses per form of severe CHD. Because of this reason, plus the fact this concerns a pilot study, we chose to include 10 fetuses per form of severe CHD. Because of this low incidence, collaboration with more than one center is needed. We believe that we will be able to collect data of the fECG of 10 fetuses with the support of the other centers.

The fECG signals are stored and digitized by a program named the NEMO system^1^. More details can be found in chapter 4.

With the collected data, we will perform several sub-analyses. We will calculate the normal values and ranges of the amplitudes (P, QRS, T), and the segment intervals with 95% confidence intervals. We will also evaluate the heart axis of the fetus. This data will be compared with the collected data of the fetuses with CHD. The patients will not be notified of any abnormal findings on the fECG, because this contains a pilot study and any findings on the fECG are still being evaluated. Therefore, this research does not have any consequences for the standard care plan of the patients and their fetuses.

If any of the fECG turns out to be abnormal, it will not influence the treatment of the fetus. The main reason for the last fact is that we do not know if the findings we think are abnormal are actually abnormal. This is one of the aspects we would like to investigate.

In the future, a longitudinal research is needed to determine the sensitivity and specificity of fECG.

Approximately 10 weeks postpartum, the patients from the cross-sectional study will receive a questionnaire about their delivery and their newborn and patient information can be withdrawn from the postnatal clinic or the attending pediatrician. If the participants do not return the questionnaire, they will be excluded from further analyses.

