## Sample size calculation

This will be the first study to investigate the clinical contribution of fECG for the diagnosis of severe CHD. We believe that a total of 200 patients will be enough to evaluate the normal range or value of the different segment intervals and amplitudes of the fECG, as described in the literature by Douglas G. Altman^10^. For the case-cohort study, we believe that a total of 10 patients per severe CHD will be enough for the evaluation and the comparison of the fECG of a healthy fetus and the fECG of a fetus with known severe CHD. No sample size calculation was used in the estimation of the size of the population for the case-cohort study, since this is a pilot study.

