# 6. METHODS

## Study parameters/endpoints

### Main study parameter/endpoint

In the cross-sectional study, the main study parameter is the determination of the normal value or range of amplitude and segment intervals with 95% confidence intervals of the fECG of a healthy fetus.

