## Study procedures

All the patients will undergo a non – invasive, transabdominal fECG during regular outpatient clinic appointments, performed by one of the researchers. This test has a very low grade of discomfort for the patient. The conducted fECG will be stored on an external hard drive, the data will be analyzed by researchers of the Technical University. The last two investigators will look at the fECG and will determine the segment intervals, the heart axis and the amplitudes. After the analysis, we will be able to enter the data in SPSS to conduct normal values and ranges with 95% confidence intervals. The patients will not be notified of any abnormal findings on the fECG, because this is a pilot study. We do not know for certain that any abnormalities we find are actually real abnormalities. This is something we want to investigate.

In the cross-sectional study, we want to know if the fetuses we included are born healthy. Therefore, we will evaluate this with a simple questionnaire which we will send four to six weeks postpartum. We believe this questionnaire will be sufficient to evaluate if any severe CHD was present at birth, because a severe CHD has hemodynamic consequences which present early in neonatal life. Besides, we have permission to withdraw patient information at the postnatal clinic or attending pediatrician. If the neonate has a congenital heart disease missed by the SEO, we will exclude the patient from the cross-sectional study and will evaluate the data of the fECG in the case-cohort study. If the participants do not return the questionnaire, they will be excluded from further analyses.

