# 8. STATISTICAL ANALYSIS

The collected data will be analyzed through SPSS 19 and two different outcome values will be calculated. The different outcome values are:

- Mean and standard deviation of segment intervals (PQ, QRS, ST etc.) with 95%

confidence intervals

- Mean and standard deviation of amplitudes of the P – top, QRS complex and the

T – top with 95% confidence intervals.

- The heart axis of the fetus

After analysis of these sub-groups (fetuses with the same form of severe CHD in one group, all the healthy fetuses in one group) in SPSS, the different intervals of the fECG of the cross-sectional study and the case-cohort study will be compared with one another through a t-test or a Mann-Whitney-Wilcoxon-test to investigate whether or not there is a repetitive pattern to be recognized. This depends from the normal distribution and the quantity of the collected data. The research is quantitative.

The questionnaires will be analyzed. We will evaluate per fetus if the conducted data from the cross-sectional population is usable and if the data of this particular patient should be excluded due to a missed diagnosis of congenital heart disease during the pregnancy.

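### The primary aim is a normal range in healthy fetuses, but the primary analysis is fixed as mean, SD and 95% confidence intervals, and no reference limits are defined

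*Protocol*

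**What the plan says.** The aim is a range. Protocol section 2 gives the primary objective as "To establish the normal ranges or values of amplitudes, segment intervals (with 95% confidence intervals) and the heart axis of the fECG", and section 6.1.1 gives the main endpoint as "the determination of the normal value or range of amplitude and segment intervals with 95% confidence intervals". The Summary explains why: normal ranges are needed before abnormalities can be detected.

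The analysis is a set of means. Section 8 lists "Mean and standard deviation of segment intervals (PQ, QRS, ST etc.) with 95" per cent confidence intervals, and the same for amplitudes. Section 8.1 repeats this as the primary parameter: "The mean and standard deviation of the segment intervals and the amplitudes (with 95% confidence intervals".

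Other places mention ranges, but only together with confidence intervals. Section 3 has "We will calculate the normal values and ranges of the amplitudes (P, QRS, T), and the segment intervals with 95% confidence intervals", and section 6.3 says the researchers will "enter the data in SPSS to conduct normal values and ranges with 95% confidence intervals".

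On the number of fetuses, section 4.4 states "We believe that a total of 200 patients will be enough to evaluate the normal range or value of the different segment intervals" and cites a textbook. Section 3 adds "With this amount of patients, we can determine with the wanted accuracy what the normal values and 95% CI of a healthy fetus are". No numerical accuracy is given.

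The distribution of the data is mentioned once, in section 8, for the choice between a t-test and a Mann-Whitney-Wilcoxon test.

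**The concern.** A normal range is a pair of limits that contains a stated share of healthy individuals. A confidence interval for a mean says how well the average is known. It narrows as more fetuses are recorded, whereas a reference interval settles at the spread of the population. The phrase in section 3 about the CI of a healthy fetus mixes the two, because an individual fetus has no confidence interval.

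This concerns the primary endpoint. Followed as written, sections 8 and 8.1 would report an average, a spread and the precision of the average, and would stop before the limits that sections 2 and 6.1.1 call for. The claim that 200 fetuses suffice is also attached to the wrong quantity, since the precision of a reference limit is never stated.

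The shape of the distribution matters as well. A t-test at n = 200 is fairly tolerant of skewness, but limits in the tails are not. The protocol checks normality for the former and is silent on the latter.

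**Working it through.** **The plan's own figure.** The 200 in section 4.4 cannot be reproduced: no SD, target precision or formula is given. The check below asks what 200 delivers, in units of the between-fetus SD.

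**Inputs.** n = 200 (sections 3 and 4.4) and the 95% level (sections 2, 6.1.1, 8 and 8.1). Normality is assumed unless stated otherwise.

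**1. Confidence interval of the mean.** Half-width = t(0.975, 199)/√200 = 1.972/14.142 = 0.139 SD.

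**2. Share of healthy fetuses inside it.** 2Φ(0.139) − 1 = 0.111, so about 89% lie outside.

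**3. Reference interval.** Half-width = 1.96 SD, with 5% outside by construction. Ratio to step 1: 1.96/0.1394 = 14.1.

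**4. Precision of a normal-theory limit (mean ± 1.96 SD).** SE = SD × √(1/n + 1.96²/(2n)).
- n = 200: √(0.00500 + 0.00960) = 0.121 SD, so the 95% CI is ±1.96 × 0.121 = ±0.24 SD.
- n = 140: √(0.00714 + 0.01372) = 0.144 SD, so ±0.28 SD.

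The 140 is an assumption (30% loss). Sections 3 and 6.3 exclude women who do not return the questionnaire, but no return rate is given. Intermediate cases are ±0.25 SD at 180 and ±0.26 SD at 160.

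**5. Precision of an empirical centile.** SE = √(p(1 − p)/n)/f, where p = 0.025 and f is the density at the limit, 0.0584 for a standard normal.
- n = 200: √(0.025 × 0.975/200) = 0.01104; 0.01104/0.0584 = 0.189 SD; 95% CI ±0.37 SD.
- Only 200 × 0.025 = 5 observations are expected beyond each limit. The order-statistic 95% CI for the 2.5th centile runs from about the 1st to the 11th ordered value.

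**6. Mean ± 1.96 SD when the data are skewed.** The documents give no distribution, so this is illustrative. For lognormal values with log-SD 0.25, 0.50 and 0.75 (assumed), 4.1%, 4.6% and 4.5% of healthy values fall above the upper limit, and 0.4%, 0% and 0% below the lower one, against an intended 2.5% on each side.

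**The case against.** The best case for the protocol has four parts.

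- **The SD is listed.** It describes spread between fetuses, so mean ± 1.96 SD follows at once from the planned outputs if the data are normal. This stands, and it means the listed outputs do more than describe the precision of the average. But no section says the step will be taken, or what happens if normality fails.
- **Ranges are promised.** Sections 3 and 6.3 say ranges will be calculated, and the wording can be read as ranges reported with confidence intervals. Section 2 also says ranges or values, and a mean does supply a value. The intention is therefore clear enough. However, no passage says how a range is formed, sections 8 and 8.1 attach the interval to the mean and SD, and the Summary's rationale needs ranges.
- **The term may be loose.** Section 3 may use 95% CI for the spread of individuals. Even so, the text needs correcting, because the sample-size claim rests on it.
- **Detail may sit in a statistical analysis plan.** The calculation method could. But the protocol itself names the primary parameter, and that does not match the objective.

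Some stronger readings are tempting and are not supported. A reader might infer that 89% of healthy fetuses will be labelled abnormal, but no passage says cut-offs will be taken from the confidence interval, and sections 3 and 6.3 say findings are neither disclosed nor used in care. A reader might infer that the CHD comparison depends on these limits, but section 8 compares measured values between groups by a t-test or rank test. A reader might argue that amplitudes must be skewed because they cannot be negative, but the documents do not say that they are unsigned. Nor are the recordings wasted: section 10.1 keeps the data for 15 years, so limits remain computable.

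**Conclusion.** The point holds as a mismatch between the primary objective and the primary analysis. The objective is a normal range. The stated output is mean and SD with 95% confidence intervals, and section 3 names a confidence interval as the target for a healthy fetus. The two intervals differ about 14-fold at n = 200 (±0.139 SD against ±1.96 SD). The figure of about 89% outside measures what would follow from reading one as the other, under normality; it is not a forecast of a planned step.

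This is more than missing detail, because the protocol fixes a primary quantity that is not the one it sets out to establish. It is also easily repaired, since the SD is already among the outputs. The precision figures rest on normal data and on the number of analysable fetuses, and the protocol does not give the expected loss from unreturned questionnaires.

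**What to change.** - **Sections 8 and 8.1:** define the primary output for intervals and amplitudes as the 95% reference interval (2.5th and 97.5th centiles), each limit with its own 95% CI. Use mean ± 1.96 SD where normality holds on the original or a transformed scale, and empirical centiles otherwise. Keep mean and SD as descriptive output.
- **Sections 2, 3, 6.1.1 and 6.3:** replace the confidence-interval wording, including the section 3 phrase about the CI of a healthy fetus, by 95% reference limits with confidence intervals. Sections 2 and 6.1.1 contain no mean or SD wording, so only that phrase changes there.
- **Sections 3 and 4.4:** state the precision with its conditions: about ±0.24 SD per limit for normal-theory limits with 200 analysable fetuses, about ±0.28 SD if 140 remain (an assumed loss), and about ±0.37 SD for empirical centiles of normal data at 200.

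The heart axis is also part of the primary parameter; this change does not supply a definition for it.

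The cost is protocol wording and a little more analysis. No new recordings, visits or participants are needed. The downside is that the stated precision will look wider than a confidence interval for a mean.

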## Secondary study parameter(s)

The typical patterns of the fECG of fetuses with a known severe CHD.

#

#

# ETHICAL CONSIDERATIONS

## Regulation statement

This study will be conducted according to the principles of the Declaration of Helsinki (64^th^ WMA General Assembly, Fortaleza, Brazil, October 2013) and in accordance with the Medical Research Involving Human Subjects Act (WMO).

## 9.2 Recruitment and consent

The patients of the cross-sectional study will be recruited through the gynecology outpatient clinic and through the Diagnostic center Eindhoven. The patients will receive information about the research during the appointment at the outpatient clinic, when the SEO or GUO-1 will be planned or via e-mail with the confirmation of their appointment for a SEO at the Diagnostic center Eindhoven. This information contains all the aspects and details of the research. Attached to the patient information letter, the patients will find an informed consent form. If patients have any questions, one of the researchers will answer these questions. Before the fECG will be conducted, the researcher will explain the meaning of the research again. The time of consideration will vary between different patients.

The patients of the case-cohort study will be recruited after the SEO and they will have recently discovered that their baby has a form of severe CHD. The follow up will be provided by a gynecologist at MMC Veldhoven, Radboud MC Nijmegen, AMC Amsterdam or Maastricht UMC. These specialists will ask the patients if they want to join the research. They will receive the information letter. Attached to the patient information letter, the patients will find an informed consent form. If wanted, the researcher can provide some extra information before conducting the fECG. It is important to conduct the fECG before week 24. The time of consideration will vary between different patients.

## 9.3 Benefits and risks assessment

No risks or adverse effects for the patient, the fetus or third parties are to be expected, except for a small chance of skin irritation due to adhesion of the electrodes to the skin. The electrodes used are known to be safe, since these electrodes are used in adult cardiology electrocardiograms. The electrodes are applied to the patient’s skin. The electrodes will transmit the electrical signal from the fetus heart to the processor^1^. In prior research concerning the non-invasive fECG, it was seen that the electrodes are safe^1, 6, 7^. All the used equipment is approved by the Medical Technical Service Department of the MMC in safety tests.

Because of the risk of aortocaval compression, the patient will be lying in a semi-recumbent position or a left lateral tilt position during the measurements. Aortocaval compression occurs because of the enlarged uterus compressing both the inferior vena cava and the lower aorta when lying in supine position. This will be prevented by the positions as mentioned above.

The benefits of this study are explained in chapter 1. In summary, the fECG will be used combined with the SEO to form a better diagnostic tool to diagnose severe CHD.

## 9.4 Compensation for injury

The sponsor/investigator has a liability insurance which is in accordance with article 7, subsection 6 of the WMO. As described above in paragraph 9.3, “benefits and risks assessment”, it is unlikely for any adverse advents to take place. The fECG with the non-invasive electrodes on the abdominal skin of the mother is a very safe manner of diagnosing fetal heart anomalies. In prior research, no adverse events were reported. Therefore, dispensation from statutory obligation to provide insurance was granted.

Because conducting the fECG will take more time than a regular appointment at the outpatient clinic, we will provide free parking cards for the patients.

# 10. ADMINISTRATIVE ASPECTS, MONITORING AND PUBLICATION

## 10.1 Handling and storage of data and documents

The data will be stored in a computer program named the NEMO system. This program can digitize and store the data of the fECG. The data will be coded, stored on a hard disk and will be handled with care. The patients will be numbered. Only the principal investigator will have the key to the code. The data will be kept for 15 years after termination of this study.

## 10.2 Monitoring and Quality Assurance

In this particular research, the principal investigator will monitor the conduct of the study. He will make sure that the data is kept safe and will ask for weekly updates. In case of any misunderstandings, he will be the contact person. Auditors and monitors from the Clinical Trial Centre Maastricht (CTCM) are able to evaluate measurements which have taken place in the MUMC. They are able to obtain data access only through the principal investigator and only if necessary.

## 10.3 Amendments

Amendments are changes made to the research after a favorable opinion by the accredited METC has been given. All amendments will be notified to the METC that gave a favorable opinion.

## 10.4 Annual progress report

The sponsor/investigator will submit a summary of the progress of the trial to the accredited METC once a year. Information will be provided on the date of inclusion of the first subject, numbers of subjects included and numbers of subjects that have completed the trial, serious adverse events/ serious adverse reactions, other problems, and amendments.

## 10.5 End of study report

The investigator will notify the accredited METC of the end of the study within a period of 8 weeks. The end of the study is defined as the last patient’s last visit.

In case the study is ended prematurely, the investigator will notify the accredited METC within 15 days, including the reasons for the premature termination.

Within one year after the end of the study, the investigator/sponsor will submit a final study report with the results of the study, including any publications/abstracts of the study, to the accredited METC.

## 10.6 Public disclosure and publication policy

Conform the “CCMO statement on publication policy”^11^, as well the positive as negative results will be published. Articles will be written by the principal investigators, mentioned on page 1, as well as other medical students and third parties participating in the study.

#

# 11. STRUCTURED RISK ANALYSIS

## 11.1 Potential issues of concern

*a. Level of knowledge about mechanism of action*

The fECG has been used for more research by Drs. [name], protocol ID nr. NL43294.015.13 and METC number 1307. There is enough knowledge about the fECG and there appear to be no known patho-physiological consequences for the mother and the fetus.

*b. Previous exposure of human beings with the test product(s) and/or products with a similar biological mechanism*

[name]. [name], post doc, has investigated this mechanism and has shown that the fECG is safe for patient use^1,6^. The fECG is also used for previously approved ongoing research by Drs. [name], protocol ID nr. NL43294.015.13 and METC number 1307.

*c. Study population*

The cross-sectional study requires healthy pregnant women. The physical condition of the patients is well enough to participate in the study. The case-cohort study requires healthy pregnant woman, but the fetuses have a known severe form of CHD. The condition of the mother AND the fetus will have to be stable enough to participate in the study.

If the mother is in a suboptimal condition, the fECG can still take place. Because the fECG is non-invasive with minimal mental pressure, it will not bring the patient in any risk. If in any case the fECG does bring a new diagnosis to the table, mental support will be offered.

